### Study Objectives and Endpoints

The main objective of this pilot study is to quantify exosomes from plasma and to analyze protein and RNA content in patients with sarcoma, with localized or metastatic disease. Analysis will be performed before and after surgery in localized disease and before and after first-line chemotherapy in metastatic sarcoma. Some patients may have received neoadjuvant chemotherapy with or without radiotherapy.

The secondary objectives are to:

Determine whether the initial exosome concentration, protein, and RNA profile vary in the plasma with localized or metastatic stage of the disease.Determine whether the exosome concentration as well as protein and RNA profile varies upon treatment.Determine whether the initial exosome concentration (T0) is associated with a response to treatment.Determine whether changes in exosome concentration before and after treatment are associated with a response to treatment.

The primary endpoint of the study is the quantification of exosome concentration in the blood, as well as the measurement of protein and RNA levels after exosome lysis. Measures will be performed before and after surgery in case of localized disease and before and after chemotherapy in case of metastatic disease.

The secondary endpoints will be exosome blood concentration, as well as protein and RNA concentrations measured after exosome lysis. Treatment response and tumor progression (locoregional or appearance of metastases) will be assessed by magnetic resonance imaging (MRI) or computed tomography (CT) scan using RECIST (Response Evaluation Criteria in Solid Tumors) V1.1 criteria.

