### Extracellular Vesicle Analysis

Thawed plasma samples will be processed to centrifugation at 2000 g at 4 °C for 20 minutes. Exosomes will be extracted with Total sEV Precipitation Reagent (4484450, Thermo Fisher Scientific) for 10 minutes following homogenization. Part of the EVs will be used to determine their concentration and distribution profile using Nanotracking Analysis (NS300, Malvern). The data will be analyzed using Nanosight NTA 3.2 Analytical Software (Malvern Instruments). The other part will be used for the analysis of EV contents (proteins and RNA) and stored at –80 °C. Content analysis (proteins and RNA) will be performed using Western blot analysis, enzyme-linked immunosorbent assay, and RNA sequencing (Illumina) approaches. It is expected that all collected blood will be used for extracellular vesicles and content analysis.

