### Sample Size

A total of 30 patients, for whom all samples required for the study have been collected, should be included, distributed as follows:

Group 1: 15 patients with localized disease, for whom the 4 samples required for the study were collected.Group 2: 15 patients with metastatic disease, for whom the 3 samples required for the study were collected.

These numbers will provide preliminary data before considering a larger study. The primary objective of this study is to measure the markers of interest in patients. Given that the study focuses on rare cancers and that statistical analyses are only secondary objectives, no statistical power calculation has been performed for this study. Patients for whom the total number of required samples was not achieved will be replaced.

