### Statistical Analysis

Plasma exosomes as well as exosomal protein and RNA concentrations will be described by their mean (SD) and their median (with extent). Comparison of baseline concentrations of participants with localized disease versus metastatic disease will be performed using nonparametric Wilcoxon tests. Comparison of pretreatment and posttreatment (surgical or drug) concentrations will be performed using nonparametric tests for matched data. Analyses will be carried out by subgroup (metastatic and localized) and on the whole population. Relative exosome variation before and after treatment will be compared in responders and nonresponders using nonparametric Wilcoxon tests. A Bonferroni correction will be applied to the *P* value to adjust the significance threshold during multiple comparisons.

The area under the receiver operating characteristic curve (AUC) modeling the response to treatment in function of initial exosome concentration will be plotted. AUCs with 95% CI values will be provided. The model will be adjusted to the type of disease (localized or metastatic). An exosome concentration threshold, predictive of response to treatment, will be determined. Performance (ie, sensitivity, specificity, and predictive values) associated with this threshold will be calculated. A similar approach will be followed concerning exosome concentration after treatment and delta between initial and posttreatment values. Different protein and RNA-derived markers will be analyzed. Performance associated to the absence or presence of these markers to predict response to treatment will be determined for each of the markers. Analyses will be performed under the software SAS 9.4 (SAS Institute).

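### Bonferroni, the only stated multiplicity rule, can put significance out of reach in tests within a 15-patient cohort if sequencing features join the family or few patients respond

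*Protocol article*

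**What the plan says.** The Statistical Analysis section of the protocol article names three kinds of test:

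- a rank-sum test of baseline concentrations, localized against metastatic disease;
- matched nonparametric tests of concentrations before and after treatment;
- a rank-sum test of relative exosome change, responders against nonresponders.

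Analyses are to be run in each disease group and in everyone together. The one error-rate rule is: "A Bonferroni correction will be applied to the *P* value to adjust the significance threshold during multiple comparisons". The section gives no alpha, sidedness, family or number of comparisons. The nearest figure is "AUCs with 95% CI values will be provided".

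Under Study Objectives and Endpoints, a secondary objective reads: "Determine whether the exosome concentration as well as protein and RNA profile varies upon treatment". Under Extracellular Vesicle Analysis, the content analysis "will be performed using Western blot analysis, enzyme-linked immunosorbent assay, and RNA sequencing (Illumina) approaches". Data Collection lists total exosome concentration, HSP70 exosome concentration and an unspecified number of microRNAs.

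Sample Size fixes the groups: "Group 1: 15 patients with localized disease, for whom the 4 samples required for the study were collected" and "Group 2: 15 patients with metastatic disease, for whom the 3 samples required for the study were collected". It adds that "no statistical power calculation has been performed for this study", because statistical analyses are secondary in this study.

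**The concern.** A rank test on a small sample can return only finitely many p-values, and the smallest is fixed by the sample size. Bonferroni divides alpha by the number of tests. Once the divided threshold falls below that smallest p-value, the test cannot reject, even if every patient changes in the same direction or the responders separate perfectly.

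This differs from low power, which a pilot may accept. A forced null result carries no information, yet it can be read as evidence against a marker. The Discussion says positive pilot results would lead to a nationwide study, so such a misreading could matter. The question is at what family size, and at what number of responders, the stated rule reaches this point.

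**Working it through.** **Inputs.** Sample Size gives 15 + 15 = 30, which adds up ("A total of 30 patients, for whom all samples required for the study have been collected, should be included"). There is no power figure to reproduce. Assumptions, because the article does not state them:

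- alpha 0.05 two-sided, with 0.10 two-sided as the alternative;
- the matched test is a Wilcoxon signed-rank test;
- p-values are exact, with no ties or zero differences;
- the number of responders is taken over a range.

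**Formulas.** Smallest two-sided p: signed-rank on n pairs, 2/2^n; rank-sum with r of N patients in one group, 2/C(N, r). Largest Bonferroni family in which significance is still possible: the whole-number part of alpha / p_min.

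**Paired test within one cohort (n = 15).** p_min = 2/32,768 = 6.10e-5.

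- At 0.05: 0.05 / 6.10e-5 = 819.2. Attainable up to 819 tests, not from 820.
- At 0.10: 1,638.4. Attainable up to 1,638 tests, not from 1,639.
- With normal-approximation p-values the smallest p is 6.55e-4, and the limit at 0.05 falls to 76.

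**Responder test within one cohort (N = 15, alpha 0.05).**

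| Responders | Smallest p | Largest family |
|---|---|---|
| 1 | 2/15 = 0.133 | none, even uncorrected |
| 2 | 2/105 = 0.0190 | 2 |
| 3 | 2/455 = 0.0044 | 11 |
| 4 | 2/1,365 = 0.00147 | 34 |
| 5 | 2/3,003 = 0.00067 | 75 |
| 7 (most even split) | 2/6,435 = 0.00031 | 160 |

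At 0.10 the limits for 2 and 3 responders are 5 and 22 tests.

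**Two readings of the family that need no sequencing.**

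- Only the three responder tests on exosome change (two cohorts and the whole population): threshold 0.05/3 = 0.0167. Two responders of 15 cannot reach it (0.0190); three can (0.0044).
- Three concentrations (exosome, protein, RNA), each with 1 stage test and 3 paired tests, plus 3 responder tests: 3 × (1 + 3) + 3 = 15 tests, threshold 0.0033. Three responders of 15 cannot reach it (0.0044); four can (0.00147).

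**Planned tests that escape the limit.**

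- Paired, whole population (n = 30): p_min = 2/2^30 = 1.86e-9; attainable up to 26,843,545 tests.
- Stage comparison, 15 v 15: p_min = 2/155,117,520 = 1.29e-8; attainable up to 3,877,938 tests.
- With normal-approximation p-values these limits drop to 28,828, and to 14,741 (with continuity correction) or 16,302 (without).

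Pooling all 30 patients also eases the responder limit: 2/435 = 0.0046 with 2 responders (up to 10 tests) and 2/4,060 = 0.00049 with 3 (up to 101). A single responder of 30 still fails uncorrected (2/30 = 0.067).

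**The case against.** The strongest reply is that the article nowhere says Bonferroni-corrected rank tests are run transcript by transcript. The tests are written for concentrations and, for responders, for exosome change only. Protein- and RNA-derived markers are handled separately, by how well their presence or absence predicts response. The microRNAs in Data Collection may be a short panel, and for a short panel the paired test on 15 patients works. The family and marker list may be set out in the full protocol or analysis plan, neither of which is shown. All of this stands, and it is why the point is conditional and does not fault the article for omitting the family.

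A reader might infer that significance is impossible for any sequencing-scale profile in this trial. It is not: the 15 v 15 and n = 30 exact tests stay attainable for millions of features. A reader might also take the Introduction's figure of more than 1,200 transcripts as the planned number of tests. It is background from preclinical work on Ewing sarcoma cells, and at two-sided 0.10 a family of 1,200 would be within the n = 15 limit anyway.

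The objection does not remove the mismatch. A profile objective and a sequencing assay are stated, within-cohort analyses are stated, and Bonferroni is the only rule offered. Either the profile falls under it, and within-cohort significance may be unattainable, or no stated rule covers it. The pooled paired test is not a full substitute, because it mixes change after surgery with change after chemotherapy.

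**Conclusion.** The point holds conditionally and is limited to tests within a cohort of 15. At two-sided 0.05 with exact p-values, the paired test cannot reach significance in a family of 820 or more tests (1,639 or more at 0.10). The responder test on exosome change cannot do so beyond 2 tests with 2 responders, or beyond 11 with 3. Whether these limits are met depends on the number of markers, alpha and the number of responders, none of which the article states.

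The documents do not support saying that the RNA-profile objective is bound to fail or that the pilot would discard every marker. Descriptive statistics and AUCs are planned, the primary objective is measurement, and nothing makes Bonferroni significance the criterion for taking a marker forward. The change is worth making because it costs little and prevents a forced null result from being misread.

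**What to change.** Replace the Bonferroni sentence with a two-part rule.

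1. **Short fixed family.** Total exosome concentration, HSP70 exosome concentration, total protein, total RNA and any microRNAs named in advance, tested with Holm. Holm gives the same familywise guarantee and is never less powerful than Bonferroni.
2. **Sequencing and protein profile.** Declare it exploratory. Use a paired moderated model for the before/after comparison (patient as block, variance shrinkage across features), Benjamini-Hochberg control of the false discovery rate, and effect sizes with confidence intervals. Both parts matter. With the rank test kept and 1,200 features as an illustration, Benjamini-Hochberg at 5% would need at least two features at the smallest p (6.10e-5 exceeds 1 × 0.05/1,200 = 4.17e-5 but not 2 × 4.17e-5 = 8.33e-5). The moderated model does not have the rank test's fixed smallest p.

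Holm's first step uses the same alpha/m threshold as Bonferroni, so it does not rescue a responder test with very few responders. Report those contrasts as estimates with confidence intervals, and state that non-significance there is not evidence against a marker.

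The cost is protocol or analysis-plan wording and a standard RNA-sequencing pipeline; no patient, sample or visit changes. The downside is that profile results carry a false discovery rate and not a familywise guarantee, which suits a hypothesis-generating pilot.

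### The stated Bonferroni correction is valid, but Holm's step-down form gives the same familywise error control with never less power, so naming Holm would be a free, minor improvement

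*Protocol article*

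**What the plan says.** The Statistical Analysis section of the protocol article sets out three kinds of test.

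- By stage: "Comparison of baseline concentrations of participants with localized disease versus metastatic disease will be performed using nonparametric Wilcoxon tests".
- Before versus after treatment: these "concentrations will be performed using nonparametric tests for matched data".
- By response: "Relative exosome variation before and after treatment will be compared in responders and nonresponders", again with Wilcoxon tests.

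The measures are introduced with "Plasma exosomes as well as exosomal protein and RNA concentrations will be described", which gives three bulk quantities. Replication across populations follows from "Analyses will be carried out by subgroup (metastatic and localized) and on the whole population".

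The multiplicity rule comes last: "A Bonferroni correction will be applied to the" P value "to adjust the significance threshold during multiple comparisons". No step-down form is named, so the ordinary reading is the single-step rule with every P value held to alpha/m. Alpha, m and the membership of the family are not given. Confidence intervals are mentioned only for the AUCs.

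The Sample Size section sets 15 patients with localized and 15 with metastatic disease. It calls the data preliminary, treats statistical analyses as secondary objectives, and reports that no power calculation was made.

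**The concern.** Single-step Bonferroni keeps every test at alpha/m even after other hypotheses in the family have been rejected. Holm relaxes the threshold after each rejection, gives the same familywise guarantee, and needs no assumption about dependence. Choosing the single-step rule therefore gives up some power without buying tighter guaranteed error control.

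This matters most when several effects are present together. That is what the article's Results section expects: differences by stage in concentration, protein and RNA profiles, and also changes with treatment. The three bulk measures come from the same isolate, so their effects may well occur together. With 15 patients per cohort, any power that can be kept at no cost is worth keeping. At stake is how many of several real differences are declared, not whether any is found.

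**Working it through.** **Inputs.** From the article: 15 and 15 patients, three bulk measures, the three kinds of test, and up to three populations (localized, metastatic, whole). Assumed, because the article gives none: familywise alpha 0.05 two-sided; standardized shifts of 0.8 to 1.2 SD (two-sample) and 0.6 to 1.0 SD of the change (paired); correlation between measures 0 to 0.7; and an 8 versus 22 responder split where one is needed. There is no stated power or derived sample size to reproduce.

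**Size of the family.** With one before/after pair per patient: 3 baseline tests + 3 measures × 3 populations = 9 before/after tests + 1 to 3 responder tests = 13 to 15. The Bonferroni threshold is then 0.05/13 = 0.0038 to 0.05/15 = 0.0033. Four and three samples per patient could add more.

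**Bonferroni is valid.** For m independent tests the familywise error is 1 − (1 − 0.05/m)^m. For m = 3 this is 0.0492 and for m = 9 it is 0.0489, against 0.143 and 0.370 uncorrected.

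**Why Holm dominates.** Order the P values. Bonferroni compares each with alpha/m. Holm compares the i-th smallest with alpha/(m − i + 1) and stops at the first failure. No Holm threshold is below alpha/m, so each Bonferroni rejection is also a Holm rejection; this held in every simulated data set. For m = 3 the Holm thresholds are 0.0167, 0.025 and 0.05. The normal-approximation power of one 15 v 15 comparison at a 1.0 SD shift is 0.635, 0.690 and 0.782 at those levels. The smallest P value faces alpha/m under both rules, so the first rejection is no easier with Holm.

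**Average power over the true effects** (simulation, exact rank tests, 15 per cohort except the 8 v 22 runs):

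| Setting | Bonferroni | Holm | Gain (points) |
|---|---|---|---|
| m = 3, one true, 1.0 SD, correlation 0.5 | 0.572 | 0.572 | 0 |
| m = 3, two true, same | 0.566 | 0.594 | 2.8 |
| m = 3, three true, same | 0.551 | 0.629 | 7.8 |
| m = 9 two-sample, three true, 0.8 SD, correlation 0 | 0.206 | 0.212 | 0.6 |
| m = 9 two-sample, three true, 1.2 SD, correlation 0 | 0.572 | 0.597 | 2.5 |
| m = 9 two-sample, all true, 0.8 SD, correlation 0 | 0.208 | 0.240 | 3.2 |
| m = 9 two-sample, all true, 1.2 SD, correlation 0 | 0.570 | 0.726 | 15.6 |
| m = 9 stage and before/after, six true, 1.2/1.0 SD | 63–68% | 69–75% | about 6–7 |
| m = 12 (adds whole-population before/after), before/after only, 0.8 SD | 53.6% | 61.8% | 8.2 |
| m = 12, all true, stage 0.8, before/after 0.6 SD | 26.4% | 31.7% | 5.3 |
| m = 12, all true, stage 1.2, before/after 1.0 SD | 68.5% | 85.5% | 17.0 |

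Across all m = 3 settings, including paired n = 15 and 8 v 22, the gain was at most 0.4 points with one true effect, about 2 to 4 with two (run for 15 v 15 and paired only), and about 5 to 9 with three. At m = 3, 1.0 SD and correlation 0.5, the chance of finding all three rose from 0.276 to 0.446.

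**What does not change.** In that last setting the chance of at least one true detection was 0.812 under both rules. In the other settings with two or more true effects it moved by at most 0.002.

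**Error control.** Under the complete null the two rules gave identical familywise error (0.046 and 0.052 at m = 3, 0.046 and 0.032 at m = 9; the 0.052 is within simulation error of 0.05). With some true effects Holm uses more of the allowance, for example 0.037 against 0.030, but its highest value in any mixed setting was 0.046.

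**The case against.** The strongest reply is that Bonferroni is a legitimate, conservative rule in a pilot whose inference is secondary and unpowered, so nothing has been stated wrongly. That stands, and it is why the point is minor. It does not remove the point: a method has been named, and a dominating one is available at no cost.

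A reader might infer that real differences will be lost for nothing. The documents do not support that. Holm recovers nothing unless another hypothesis is rejected first, and it does nothing for a lone effect.

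A reader might also confine the point to a small family of bulk measures. The article does not define such a family. The correction sentence directly follows the responder comparison, and the listed tests already number 13 to 15.

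A third tempting inference is that markers would drop out of the nationwide study. The article ties that study only to success or positive results, not to adjusted significance, and descriptive summaries and AUCs with intervals are reported in any case.

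Finally, the article condenses a fuller protocol. Single-step is the ordinary reading of its wording but is not spelled out. If the full document already uses a step-down form, only the article's wording needs changing.

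**Conclusion.** The point holds as a minor efficiency improvement. Bonferroni controls the error as intended. Holm controls it at the same level under any dependence and never rejects less. The usual reason to keep the single-step rule, its simple matching simultaneous intervals, does not apply because none are planned for these tests.

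The size depends on how many effects are real: about nil with one; about 1 to 4 points of average power with two of three or three of nine; 6 to 8 points when most of a 9- or 12-test family is real; and about 3 to 17 points when all are. The top of that range is a best case with shifts of 1.0 to 1.2 SD throughout. All figures rest on the assumed alpha, shifts, correlations and, where used, responder split. That Holm dominates rests on none of them.

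**What to change.** In the Statistical Analysis section, replace the Bonferroni correction with the Holm step-down (sequentially rejective Bonferroni) correction. Apply it to the whole set of comparisons the present sentence covers: baseline by stage, before/after treatment by subgroup and overall, and responders versus nonresponders. Report Holm-adjusted P values: for the i-th smallest, the maximum over j ≤ i of min(1, (m − j + 1) × p(j)).

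The cost is one changed phrase. No patients, samples or assumptions are added, the familywise guarantee is unchanged, and SAS 9.4, the software named in the plan, computes the adjusted values directly. As with Bonferroni, the number of comparisons must be fixed before the analysis.

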## Results

This study is expected to provide valuable insights into the role of exosomes in sarcomas, both in localized and metastatic stages. We anticipate that exosome concentration, as well as protein and RNA profiles, will differ between localized and metastatic disease, reflecting distinct tumor biology. Furthermore, we expect to observe variations in exosome concentration and content before and after treatment, potentially correlating with treatment response. A higher baseline exosome concentration may be associated with a poorer or more aggressive disease profile, while changes in exosome levels following treatment could serve as predictive biomarkers for therapeutic efficacy. The integration of exosome analysis with imaging-based assessments (MRI or CT scan using RECIST V1.1 criteria) will help establish correlations between exosome dynamics and tumor progression. If confirmed, these findings could pave the way for the use of exosomes as noninvasive biomarkers for monitoring sarcoma treatment response and disease progression, ultimately improving patient management.

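### The response AUC is read from a model fitted and evaluated in the same 15 to 30 patients, so 0.50 is not its no-information value and a corrected or reference AUC should stand beside it

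*Protocol article*

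**What the plan says.** The Statistical Analysis section plans an AUC "modeling the response to treatment in function of initial exosome concentration will be plotted", with a 95% CI, from a model that also contains disease type (localized or metastatic). It then extends the method: "A similar approach will be followed concerning exosome concentration after treatment and delta between initial and posttreatment values". A threshold with sensitivity, specificity and predictive values follows. The section mentions neither how the curve is oriented nor any correction for evaluating the model on its own data.

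Under Sample Size: "A total of 30 patients, for whom all samples required for the study have been collected, should be included", split into 15 with localized and 15 with metastatic disease. The first paragraph of Statistical Analysis adds: "Analyses will be carried out by subgroup (metastatic and localized) and on the whole population". No response rate is stated anywhere.

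On direction, the Results section offers one sentence: "A higher baseline exosome concentration may be associated with a poorer or more aggressive disease profile". It gives no direction for the posttreatment value or for the change. The secondary objectives ask only whether concentration, or its change, is associated with response. They do not say which way.

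**The concern.** An AUC from a fitted model ranks patients by predicted response. The model estimates from the same patients whether high or low exosome levels go with response, and it estimates the disease-type effect at the same time. The score is thereby turned towards a value above 0.50 whichever way the marker happens to run. Disease type can lift it further with no help from the exosomes.

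A reader will naturally compare the AUC with 0.50. In samples of 15 or 30 the gap between 0.50 and what a useless marker yields is not negligible. This matters because the Discussion makes a nationwide study conditional on positive results here, and the AUC is the main summary of predictive value. The Bonferroni correction acts on P values and does nothing to an AUC estimate.

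**Working it through.** The article states no AUC, power or precision figure, so there is nothing of its own to reproduce. The check asks what AUC a marker unrelated to response would show.

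**Inputs.** From Sample Size: 30 patients, 15 per group. Assumed, because the article gives no rate: 20 to 50% responders, i.e. 6 to 15 of 30, or 3 to 7 of 15.

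**Step 1: marker alone, direction taken from the data.** With n1 responders and n0 nonresponders, a useless marker's empirical AUC has mean 0.50 and SD = √[(n + 1)/(12·n1·n0)]. If the data choose the direction, the reported value is max(AUC, 1 − AUC), with mean approximately 0.5 + √(2/π)·SD.

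- 10 of 30: SD = √(31/2400) = 0.114; mean = 0.5 + 0.798 × 0.114 = 0.591.
- 5 of 15: SD = √(16/600) = 0.163; mean = 0.5 + 0.798 × 0.163 = 0.630.

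Simulation (20,000 runs per row):

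| Responders | Mean, direction fixed beforehand | Mean, direction from data |
|---|---|---|
| 15 of 30 | 0.500 | 0.585 |
| 10 of 30 | 0.501 | 0.591 |
| 6 of 30 | 0.500 | 0.608 |
| 7 of 15 | 0.503 | 0.624 |
| 5 of 15 | 0.498 | 0.633 |
| 3 of 15 | 0.500 | 0.657 |

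A one-marker logistic model actually fitted to such data (4,000 runs) gives 0.58 to 0.65 for a normally distributed marker and 0.57 to 0.63 for an unlogged lognormal one. The shortcut is therefore a fair proxy, slightly high for a skewed marker.

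The chance that a useless marker reaches 0.70 roughly doubles: from 0.042 to 0.080 with 10 of 30 responders, and from 0.127 to 0.259 with 5 of 15. The 0.70 mark is a yardstick chosen here; the article sets none.

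**Step 2: the model the plan names, with disease type, n = 30 (15 + 15), useless marker (4,000 runs).**

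| Response by disease type | Disease type alone | Type plus useless marker |
|---|---|---|
| Identical counts in both types | 0.500 | 0.58 to 0.61 |
| Equal true rates of 50%, chance imbalance allowed | – | 0.63 |
| Equal true rates of 33% | – | 0.64 |
| Equal true rates of 20% | – | 0.67 |
| 10/15 versus 5/15 | 0.667 | 0.708 |
| 12/15 versus 4/15 | 0.768 | 0.803 |

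The type-alone figures can be checked by hand. With 10/15 versus 5/15, two thirds of responders and one third of nonresponders are in the better type, so AUC = (2/3 + 2/3)/2 = 0.667. With true rates of 33% and 67% and counts left to chance, the adjusted model averages about 0.72.

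**Step 3: does the planned 95% CI protect the reader?** For the marker alone, changing the direction does not alter how often a two-sided CI excludes 0.50: 6.9% (10 of 30), 9.9% (5 of 15) and 14.8% (3 of 15) in either orientation. For the adjusted model with a useless marker and equal true rates of 20 to 50%, the CI excludes 0.50 in about 18 to 24% of runs.

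**Step 4: after the change.** With orientation fixed beforehand, a useless marker's AUC stratified by disease type averages 0.50 in every setting tried.

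**The case against.** The strongest reply is that the article is a condensed account. Orientation and optimism correction may sit in the full protocol or the analysis plan, neither of which is shown. That the data set the direction is inferred from the planned modeling. This limits the point but does not remove it: the article states a method, and that method, followed as written, gives an apparent AUC that is biased upward.

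A reader might infer something stronger: that the article states an expected direction for response and the analysis ignores it. The documents do not support that. The Results sentence is hedged, concerns disease profile rather than treatment response, and covers baseline only. The objectives are direction-neutral, so a two-sided analysis fits them.

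Nor would a marker running the opposite way necessarily go unnoticed. A threshold with its sensitivity and specificity has to say which side predicts response, and the responder comparison shows the direction of change.

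The CI argument is correct for a marker alone. It fails for the adjusted model in the plan, as Step 3 shows.

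Two further limits stand. The subgroup sentence belongs to the paragraph on nonparametric tests, so applying it to the ROC analysis is a reading, and the figures for 15 patients depend on it. Replacing the model with a raw-marker AUC would discard the planned disease-type adjustment.

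**Conclusion.** The point holds in this form: as planned, the response AUC is an apparent value whose no-information level lies above 0.50. Assuming 20 to 50% responders, that level is about 0.59 to 0.61 for a marker alone in 30 patients and about 0.62 to 0.66 if run in 15. For the disease-type-adjusted model in 30 patients it is about 0.63 to 0.67 with equal true response rates. It is higher if response differs by type, and the reference is then the AUC of disease type alone plus the optimism. All ranges move with the response rate, which the article does not give.

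The finding does not rest on any stated hypothesis about direction; the bias arises whether or not one exists. It affects secondary analyses in a pilot described as preliminary, so it does not threaten the study. It does merit correction, because these AUCs will inform the decision on a larger study and the remedy is cheap.

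**What to change.** Keep the disease-type-adjusted model. For the baseline value, the posttreatment value and the delta, report beside each apparent AUC:

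- either an optimism-corrected AUC or the permutation no-information AUC, obtained by shuffling the marker within disease type, refitting and averaging;
- the AUC of disease type alone;
- the sign of the exosome association.

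Bootstrap correction or permutation is the safer choice. Leave-one-out is also possible, but pooling its predictions into one AUC can overcorrect and push a useless model below 0.50 at this sample size.

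Optionally, add a marker AUC stratified by disease type, with the orientation for each marker fixed before analysis and values below 0.50 shown as they fall. The authors would have to choose those orientations, since the article suggests one only for baseline and only for disease profile.

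The cost is a sentence or two in the analysis section, a little more programming, and lower corrected AUCs. No extra patients or samples are needed.
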